Faced with COVID-2019, because of no clinically specific drugs currently[19], doctors choose the drugs mentioned above empirically but the clinical efficacy is unsatisfactory and uncertain. During these challenging and unprecedented times, the current clinical guideline in China suggest both conventional medicine and TCM should be used for the treatment of patients with infection of SARS-CoV-2[20].

Based on these evidence and experience, there is a general expectation that TCM would be a valuable weapon in the armory against SARS-CoV-2. So an open-label, multicenter randomized controlled study will be carried out to evaluate the efficacy and safety of Traditional Chinese Medicine in treating COVID-2019. This study is conducted in Wenzhou city, Zhejiang Province, because Wenzhou is one of the worst-hit cities outside hubei province by COVID-2019.

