**Exclusion criteria**

1. < 18 or > 85 years old.
2. Pregnancy and lactation.
3. Serious heart, liver, kidney and hematopoietic system diseases, abnormal liver or kidney function.
4. Suffering from other known virus pneumonia.
5. Allergic to Chinese herbal medicine or suffering from allergies.
6. Critical patients ( respiratory failure treated by mechanical ventilation or shock or multiple organ failure).

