**Blinding**

Because of the odor and color of traditional Chinese medicine decoction, the patients and clinical therapists will be unblinded in this trial. But the outcome assessors and data analysts will be blinded throughout the entire study.

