**INTERVENTIONS**

Maxingshigan-weijing decoction consists of 10 g of Herba Ephedra (Mahuang), 10 g of Amygdalus Communis Vas (Xingren), 45 g of Gypsum Fibrosum (Shigao), 30 g of Rhizoma phragmitis (Lugen), 20 g of Peach kernel (Taoren), 20 g of Winter Melon kernel (Dongguaren), 30 g of Trichosanthes Kirilowii Maxim (Gualou), 12 g of Pericarpium Citri Reticulatae (Chenpi), 12 g of Rhizoma Pinelliae (Jiangbanxia), 12 g of caulis bambusae in taeniis (Zhuru), 30 g of semen lepidii (Tingliz), 15 g of semen lepidii (Shichangpu), 10 g of curcuma zedoary (ezhu) and 5 g of Radix Glycyrrhizae (Gancao). Maxingshigan-weijing decoction will be prepared by TCM pharmacy of the First Affiliated Hospital of Wenzhou Medical University.

Inpatients will be randomly assigned to two groups receiving either Routine supportive care alone which includes Stay in bed, Nasal cannula of oxygen therapy, broad-spectum antibiotics and antivirals, or the combination of Maxingshigan-weijing decoction for continuous 14 days, 200 mL twice a day at 10 AM and 4PM. All participants will be hospitalized so that they could be quarantined and closely observed. What is more, to ensure compliance with the medication, patients will be asked to return the empty wrapping papers. If there will be any remaining medicine, it will be recorded.

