***Secondary outcomes***

**TCM Syndrome Scoring System**

### TCM Syndrome Scoring System will be used at the baseline and day 3, day 7, day 10 and day 14 of the drug intervention. It is a checklist covering 4 main, 7 secondary and 13 accompanying items. These items are the symptoms and signs summarized by experts according to the clinical manifestations of COVID-2019[24]. The main items consisting of fever, coughing, fatigue and short breath use a four-point scale (0, 2, 4 and 6) depending on the severity; the 7 secondary items including dysphoria, diarrhea, pharyngalgia, expectoration, muscular soreness, nasal obstruction and rhinorrhoea use 0-3-point scale; the 13 accompanying items contain chest pain, headache, aversion to cold, dizziness, nausea and vomiting, anorexia, abdominal distension, dry mouth, anxiety, spontaneous sweating, insomnia, wheezing and blood tinged sputum, and each item is rated on 0-1 scale ( 0 stands for asymptomatic, 1 stands for symptomatic ). The total scores sum up to a range from 0 to 58, with higher scores indicating more severe levels of disease.

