***Adverse event reporting and treating***

Adverse events (AEs) will be defined as unpredictable, undesirable symptoms, signs or diseases related to the administration of maxingshigan-weijing decoction and will be recorded and managed by the researchers during the treatment period. The researchers will scrupulously evaluate the relationship between these adverse events and the experimental drugs, then manage them quickly and properly. Furthermore, patients will be continuously followed up until their condition returns to normal. Participants who might be injured during the study will get a financial compensation.

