traditional Chinese and western medicine in the treatment of SARS.

Journal of practical internal medicine of traditional Chinese

medicine,2005.19(6):529.

1. Qing Miao, Xiaodong Cong, Bing Wang et. al. Recognition and

reflection of TCM on pneumonia caused by novel

coronavirus.2020,61(2):1-4.

2. JSM P, D P, Yuen KY ea. The Severe Acute Respiratory Syndrome. New Engl J 71. Med.. 2003; 249: 2431-41.

[figure not shown]

|  | **Pre** | **Research Phase** | | | | | | | | | | | | | | **Follow-up** | |
| --- | --- | --- | --- | --- | --- | --- | --- | --- | --- | --- | --- | --- | --- | --- | --- | --- | --- |
| **Time point** | **D0** | **D1** | **D2** | **D3** | **D4** | **D5** | **D6** | **D7** | **D8** | **D9** | **D10** | **D11** | **D12** | **D13** | **D14** | **D7** | **D14** |
| **Research activities** |  |  |  |  |  |  |  |  |  |  |  |  |  |  |  |  |  |
| Enrollment | × |  |  |  |  |  |  |  |  |  |  |  |  |  |  |  |  |
| Eligibility screen | × |  |  |  |  |  |  |  |  |  |  |  |  |  |  |  |  |
| Informed consent | × |  |  |  |  |  |  |  |  |  |  |  |  |  |  |  |  |
| Randomization | × |  |  |  |  |  |  |  |  |  |  |  |  |  |  |  |  |
| **Intervention activities** |  |  |  |  |  |  |  |  |  |  |  |  |  |  |  |  |  |
| TCM + Supportive care |  | × | × | × | × | × | × | × | × | × | × | × | × | × | × |  |  |
| Supportive care |  | × | × | × | × | × | × | × | × | × | × | × | × | × | × |  |  |
| **Baseline assessments** |  |  |  |  |  |  |  |  |  |  |  |  |  |  |  |  |  |
| Socio-demographics | × |  |  |  |  |  |  |  |  |  |  |  |  |  |  |  |  |
| Medical history | × |  |  |  |  |  |  |  |  |  |  |  |  |  |  |  |  |
| Differentiation | × |  |  |  |  |  |  |  |  |  |  |  |  |  |  |  |  |
| Routine inspection | × |  |  |  |  |  |  |  |  |  |  |  |  |  |  |  |  |
| Concomitant medication | × | × | × | × | × | × | × | × | × | × | × | × | × | × | × | × | × |
| **Outcome assessments** |  |  |  |  |  |  |  |  |  |  |  |  |  |  |  |  |  |
| Syndromes Relief | × |  |  | × |  |  |  | × |  |  | × |  |  |  | × |  |  |
| Coronavirus nucleic acid test | × |  |  | × |  |  |  | × |  |  | × |  |  |  | × |  |  |
| TCM Syndrome Scoring System | × |  |  | × |  |  |  | × |  |  | × |  |  |  | × | × | × |

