| **Safety outcomes** |  |  |  |  |  |  |  |  |  |  |  |  |  |  |  |  |  |
| Routine inspection | × |  |  | × |  |  |  | × |  |  | × |  |  |  | × | × | × |
| Urine routine test | × |  |  | × |  |  |  | × |  |  | × |  |  |  | × | × | × |
| Blood rne test | × |  |  | × |  |  |  | × |  |  | × |  |  |  | × | × | × |
| Biochemical test | × |  |  | × |  |  |  | × |  |  | × |  |  |  | × | × | × |
| Electrocardiogram | × |  |  | × |  |  |  | × |  |  | × |  |  |  | × | × | × |
| Adverse events |  | × | × | × | × | × | × | × | × | × | × | × | × | × | × | × | × |

**Fig.2** SPIRIT schedule for enrollment,treatment and assessments.

D day,TCM Traditional Chinese Medicine

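### The adverse event definition requires relatedness to the decoction, so under its literal wording control patients cannot have an adverse event

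*Protocol*

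**What the plan says.** The Protocol section Adverse event reporting and treating gives the only definition in the document: "Adverse events (AEs) will be defined as unpredictable, undesirable symptoms, signs or diseases related to the administration of maxingshigan-weijing decoction". It adds that researchers record and manage these events in the treatment period, that they assess the relationship to the study drug, and that affected patients are followed until recovery.

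Under INTERVENTIONS, one group is described as "receiving either Routine supportive care alone", so it has no exposure to the decoction. Under Blinding, "the patients and clinical therapists will be unblinded in this trial". The Background section gives the purpose of the trial as to "evaluate the efficacy and safety of Traditional Chinese Medicine in treating COVID-2019".

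Fig. 2 ("SPIRIT schedule for enrollment,treatment and assessments") has separate intervention rows by arm, one of them labelled "TCM + Supportive care". It has a single adverse event row, marked on D1 to D14 and at both follow-up visits.

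**The concern.** An adverse event count is useful for safety when the same rule applies in both arms. COVID-19 inpatients can have events caused by the disease, by antivirals and by antibiotics, and a control count is what separates that background from harm due to the decoction. If relatedness to the decoction decides what counts, the control arm supplies no background figure. The count in the treated arm then measures how often staff who may know the allocation blame the decoction.

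The requirement that an event be unpredictable adds a second filter, which removes reactions that could be foreseen. The protocol itself anticipates allergy, since it excludes patients who are "Allergic to Chinese herbal medicine or suffering from allergies". A literal reader could therefore leave an allergic reaction out.

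An analysis plan cannot repair this, because it cannot recover events that were never recorded.

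**Working it through.** The plan gives no figure to reproduce. The check compares the sections, then sizes the consequence.

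**Who can have an adverse event under the definition**

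1. An event must be undesirable, unpredictable and related to the decoction (Adverse event reporting and treating).
2. Control patients do not receive the decoction (INTERVENTIONS), so condition 1 cannot be met in that arm.
3. Allocation is 1:1 with 70 per arm (Randomization). The literal rule excludes 70 of 140 patients, or 50%.
4. No other section widens the definition or sets a rule for control-arm events.
5. Fig. 2 splits the intervention rows by arm but not the adverse event row. This suggests that events are meant to be collected from everyone, which conflicts with steps 1 to 3.

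**Recording window (minor)**

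- The text covers the treatment period: 14 of 14 + 14 = 28 days, or 50%.
- Fig. 2 has 14 marks in treatment and 2 in follow-up, so the text covers 14 of 16.
- Open events are followed to recovery, so only events first seen after D14 are left uncovered.

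**What is still collected in both arms regardless of cause**

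- Vital signs, laboratory tests and electrocardiograms (Safety outcomes).
- The TCM Syndrome Scoring System: "It is a checklist covering 4 main, 7 secondary and 13 accompanying items", so 4 + 7 + 13 = 24 symptoms. They include diarrhea, nausea and vomiting, dizziness and headache. Fig. 2 schedules it 7 times (D0, D3, D7, D10, D14 and two follow-up visits). It has no item for rash.

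**Illustration (assumed rates; the protocol gives none and plans no test of event counts)**

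Expected patients counted in the decoction arm = 70 × event rate × share attributed to the decoction. The control count is 0 by definition.

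| True rate, decoction v control | 10% attributed | 25% attributed | 50% attributed | All events recorded |
|---|---|---|---|---|
| 20% v 20% (no harm) | 70×0.20×0.10 = 1.4 v 0 | 70×0.20×0.25 = 3.5 v 0 | 70×0.20×0.50 = 7 v 0 | 14 v 14 |
| 40% v 20% (rate doubled) | 70×0.40×0.10 = 2.8 v 0 | 70×0.40×0.25 = 7 v 0 | 70×0.40×0.50 = 14 v 0 | 28 v 14 |

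An expected count of 7 v 0 appears in both rows. With every event recorded, the 95% half-width for the difference in proportions is

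- no harm: 1.96 × √(2 × 0.2 × 0.8 / 70) = 13.3 percentage points;
- rate doubled: 1.96 × √((0.4 × 0.6 + 0.2 × 0.8) / 70) = 14.8 percentage points.

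**The case against.** The best counter-argument comes from the same section. Researchers are told to judge the relationship to the drug afterwards, which would be redundant if relatedness were already an entry condition. Perhaps the wording is loose and everything is to be recorded first. That is possible, and for this reason it cannot be said that the control count will be zero in practice. But on that reading the section contradicts itself and still needs correcting.

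Other objections hold in part:

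- **Fig. 2** nowhere says that the adverse event row applies to all participants. That is inferred from the layout, and no other assessment row is split by arm either. The defect in the definition stands without the figure.
- **Discontinuation criteria** are not limited to one arm and include worsening to ventilator support whatever the cause, with data kept on the case report form. That outcome is captured; other clinical events are not. Whether serious adverse events there inherit the narrow definition is not stated.
- **Allergy** is a weak example, because a reaction in someone who passed the screen may be unforeseen for that patient. It is not needed for the main point.
- **Blinding** covers outcome assessors, and the protocol does not say which researchers record events. But the Randomization section has researchers open the allocation envelopes, so those recording events are not shown to be blinded.
- **Timing:** Version 2.0 is dated October 14, 2020, and recruitment is expected to end on December 31, 2020. A late change leaves two recording regimes in one table. This is a reason to flag earlier patients, not to keep the rule.

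**Conclusion.** The definition is wrong as written. Applied literally, it removes the whole control arm (70 of 140 patients) from adverse event counting. It also makes counts in the decoction arm depend on attribution in an open-label trial, and excludes foreseeable reactions. Clinical adverse event counts, and serious ones if they follow the same definition, cannot then be compared by arm. Events outside the symptom checklist, such as rash, have no control comparator.

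The defect goes no further. The efficacy analyses, the laboratory safety assessment and the planned t-tests on safety measurements are untouched, and the 24 checklist symptoms remain comparable. The core conclusion rests on the protocol's wording alone. The 7 v 0 illustration depends on assumed event rates and attribution shares and only shows the direction of the problem. How control events are handled in practice cannot be told from the protocol. The point should be corrected because safety is a stated aim and the correction is cheap.

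**What to change.** Replace the definition in Adverse event reporting and treating with:

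> An adverse event is any untoward medical occurrence in a randomized participant in either arm, from randomization to the second follow-up visit, whether or not considered related to treatment. Relatedness and seriousness are recorded separately and do not decide whether an event is counted.

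Report by arm the number of patients with any event and with any serious event. The new text removes the unpredictability condition and agrees with the adverse event row and follow-up marks in Fig. 2.

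The cost is two sentences and some extra recording in control patients. Recruitment began in March 2020, so records for patients enrolled before the change may be less complete. Flag those patients in the table; the protocol does not say how many there are.

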**Abstract**

**Introduction:** The outbreak of a novel coronavirus (SARS-CoV-2) and associated COVID-19 disease in late December 2019 has led to a global pandemic. It directly leads to high morbidity and mortality, but also results in a devastating effect on the global economy. Nowadays many trials are underway on this disease to evaluate the efficacy of various therapeutic remedies. This study aims at investigating the effect of Traditional Chinese Medicine, maxingshigan-weijing for treating patients with COVID-19.

**Methods and analysis:** This is an open-label, multicenter randomized controlled clinical trial. One hundred and forty patients infected by SARS-CoV-2 will be randomly assigned to the control group or the experimental group ( Traditional Chinese Medicine, TCM group ) in an equal ratio. The patients in control group will receive routine supportive clinically care including the therapies of anti-viral, anti-bacterial and ameliorating the related symptoms, while patients in TCM group will be asked to take traditional Chinese medicine, maxingshigan-weijing for consecutive 14 days in addition to supportive care. All data will be gathered at baseline and on days 3, 7, 10 and 14. The primary outcome measure will be the number of days till at least one of the clinical symptoms (fever, cough, malaise, shortness of breath) improves in the first 14 days of treatment. Secondary outcome measures will include TCM Syndrome Scoring System and the time of negative of SARS-CoV-2 nucleic acid. A laboratory test will be taken before and after treatment to assess the safety of TCM.

**Discussion:** The study may help to identify the the efficacy and safety of Traditional Chinese Medicine, Maxingshigan-weijing in treating COVID-2019.

**Trial registration:** Chinese Clinical Trial Registry, ChiCTR2000030759. Registered on March 13th 2020, <http://www.chictr.org.cn/.>

**Keywords:** SARS-CoV-2, COVID-2019, Traditional Chinese Medicine ( TCM ), Maxingshigan-weijing decoction, Randomized controlled trial, Protocol

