**METHODS**

**Study design**

This is an open-label, multicenter, randomized controlled, comprehensive treatment clinical study, with outcome assessors and data analysts blinded to the group assignment. Eligible participants with Mild and Moderate Pneumonia caused by SARS-CoV-2 will be randomly assigned to either the experimental ( Traditional Chinese Medicine + Routine supportive care ) or the control group ( Routine supportive care ) in an equal proportion. Routine supportive care remains the major treatment, including the therapies of anti-viral, anti-bacterial and ameliorating the related symptoms[21]. The study consisted of three phases: a screening period, a treatment period of 14 days, and a follow-up period of 2 weeks. Fig. 1 briefly shows the study flow chart, and Fig. 2 enumerates the treatment schedule and outcome measures. The study adheres to the Standard Protocol Items: Recommendations for Intervention Trials (SPIRIT 2013) checklist [22].

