**Criteria for discontinuing**

1. The participant decides to discontinue the intervention, the trial or data collection at any time for any reason.
2. Non-compliant patient.
3. In the case of the onset of serious adverse events.
4. The aggravating pathology changes which require ventilator support for treatment during the intervention.

Participants discontinued the trial will be recorded throughout the intervention and followup periods, their data will be collected in the case report form. If the trial wouldn’t continue due to serious adverse events or aggravated illness, appropriate treatment will be taken.

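### The adverse-event text limits recording to the 14-day treatment period, but Fig. 2 also collects events at both follow-up visits, so the window is 14 days in one place and 28 in the other.

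*Protocol*

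**What the plan says.** The protocol states when adverse events are collected in several places.

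- **Adverse event reporting and treating.** Events "will be recorded and managed by the researchers during the treatment period". The same section adds that "patients will be continuously followed up until their condition returns to normal".
- **Study design.** After screening, the trial has "a treatment period of 14 days, and a follow-up period of 2 weeks". Follow-up is thus a phase of its own and not part of treatment.
- **Fig. 2, safety outcomes.** The row labelled "Adverse events" is marked on each day from D1 to D14 and at the follow-up visits on D7 and D14. Routine inspection, urine, blood, biochemistry and electrocardiogram are also marked at both follow-up visits.
- **Criteria for discontinuing.** "Participants discontinued the trial will be recorded throughout the intervention and followup periods, their data will be collected in the case report form". Adverse events are not named there.
- **Abstract.** Data are gathered at baseline and on days 3, 7, 10 and 14, and "A laboratory test will be taken before and after treatment to assess the safety of TCM". The follow-up visits are not mentioned.

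**The concern.** The text and the figure cannot both govern. Staff who work from the adverse-event section stop entering new events when the 14 days end. Staff who work from Fig. 2 continue to the second follow-up visit. The trial recruits at three hospitals, and nothing in the protocol says which statement takes precedence.

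Assessing safety is a stated aim. An abnormal blood result or electrocardiogram first seen at a follow-up visit would be measured under Fig. 2 but, under the text, need not be entered as an adverse event. A symptom that starts in those two weeks and shows in no scheduled test might leave no record at all. An analysis plan cannot repair this, because the protocol decides what goes on the case report form and an event never entered cannot be recovered at analysis.

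**Working it through.** The protocol states no event count or rate, so there is no figure of its own to reproduce. The check sets the two windows side by side.

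**Inputs**
- Treatment period: 14 days (Study design).
- Follow-up period: 2 weeks, or 14 days (Study design).
- Adverse-event marks: D0 blank, D1 to D14 marked, follow-up D7 and D14 marked (Fig. 2). The row and the time-point header each have 18 cells, including the label cell, so the marks line up with the columns and the follow-up marks are not an effect of text extraction.

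**Assumptions:** the follow-up columns D7 and D14 count from the end of treatment, and a mark at a follow-up visit covers events since the previous contact.

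| | Adverse-event section | Fig. 2 |
|---|---|---|
| Window | D1 to D14 | D1 to D14, then follow-up to D14 |
| Length | 14 days | 14 + 14 = 28 days |
| Marks in treatment | – | 14 |
| Marks in follow-up | – | 2 |
| Total marks | – | 14 + 2 = 16 |

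Share of the Fig. 2 window with no recording under the text: (28 − 14) / 28 = 0.50.

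**Do other passages settle it?**
1. The promise to follow patients until they recover concerns events already found. It does not provide for recording a new event that starts after D14.
2. Safety outcomes says that safety is monitored during the trial. This fits Fig. 2 better than the adverse-event section but sets no window.
3. Criteria for discontinuing extends recording through follow-up for patients who discontinue. If that includes adverse events, a patient who stops early is recorded for longer than one who completes under the adverse-event section, which cannot be intended.
4. The abstract's data-collection days agree with the in-treatment laboratory days in Fig. 2 (D0, D3, D7, D10, D14) and omit only the two follow-up visits. Its phrase on laboratory tests before and after treatment is a summary and states no number of draws.

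None of these removes the conflict. The number of events lost would be the rate of new events in follow-up times the patients observed. The first factor is not given, so no number follows.

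**The case against.** The strongest reply is that one phrase disagrees with a fuller schedule, and that sensible staff would follow the schedule. The follow-up laboratory tests and electrocardiograms take place whatever the phrase says, so those abnormalities would still be measured. The only safety comparison that the protocol specifies is a t-test on each safety measurement, which the phrase does not alter. Only 2 of the 16 adverse-event marks fall in follow-up. That the hospitals would actually diverge is not shown, and trial conduct is reviewed weekly. All of this stands and limits the weight of the point. It does not remove the contradiction, since a measurement is not an adverse-event record and a symptom may show in no test.

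A reader might infer more than the documents support, in three ways.

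- **Loss after an early stop of the decoction.** It is tempting to read the treatment period as ending with a patient's last dose. The protocol does not say so. The period is a fixed 14-day phase, Fig. 2 marks D1 to D14 for both arms, and the discontinuation section says that patients who stop are "Participants discontinued the trial will be recorded throughout the intervention and followup periods" in scope. Because that section does not name adverse events, a small ambiguity remains, but there is no stated rule that ends recording early.
- **Loss in one arm, or a bias in favour of the decoction.** The window in the text is the same 14 days for both arms. The asymmetry in that section lies elsewhere, in defining adverse events as those "related to the administration of maxingshigan-weijing decoction". Read literally, that leaves a control patient with no adverse events to record, which would tilt counts against the decoction. It is a separate matter, and correcting the window does not resolve it.
- **A competing laboratory schedule in the abstract.** Counting one post-baseline draw there against six in Fig. 2 would ignore the abstract's own list of collection days.

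**Conclusion.** The point holds as an internal contradiction. The adverse-event section gives a 14-day window and Fig. 2 gives 28 days, so 14 of 28 days (50%) have events collected under one and not under the other. Followed literally, the text leaves new events in the two-week follow-up unrecorded.

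The 28-day figure rests on the two assumptions stated with the calculation. The contradiction itself does not, because the figure marks adverse events at visits outside the treatment period on any reading. How many events are affected is unknown.

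This is a correction of moderate weight. It affects the completeness of the safety record and leaves the primary endpoint, randomisation and sample size untouched. The documents do not support a claim of differential loss between arms or of a direction of bias.

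**What to change.** Reconcile the adverse-event section with Fig. 2. Replace the reference to the treatment period with one calendar window for all randomised patients in both arms, from the start of treatment (D1) to the second follow-up visit (follow-up D14), whether or not the decoction is still being taken. This also closes the small ambiguity about patients who discontinue. Keep the existing provision for following open events to recovery.

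As a minor consistency edit, bring the abstract's data-collection and laboratory wording into line with the Fig. 2 days, including the two follow-up visits.

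The cost is wording and a few more case report form entries, since Fig. 2 already schedules the visits and tests. One limit should be stated: recruitment began in March 2020 and this version is dated October 2020, so new wording cannot by itself restore events that were not entered for patients already through follow-up. The sponsor should establish which window was applied to them and report it.
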